# Effects of digital health education intervention on stress, anxiety and depression of patients with polycystic ovarian syndrome: study protocol for a single blinded randomized controlled trial

**DOI:** 10.3934/publichealth.2026007

**Published:** 2026-01-09

**Keywords:** polycystic ovarian syndrome, depression, anxiety, stress, mHealth, digital health education

## Abstract

**Background:**

Polycystic ovarian syndrome (PCOS) is an endocrine disorder that is connected to a range of gynecological symptoms. The disorder has both physical and mental health outcomes. While the physical symptoms are often expressed and diagnosed, the mental health outcomes are ignored and undiagnosed. To the best of our knowledge, in Bangladesh, although women are affected by the disease, research exploring the impact of digital health interventions on the mental health burden is scarce. Emerging evidence suggests that smartphone-based health education interventions could be helpful in alleviating the psychological burden associated with PCOS by improving awareness and self-management among patients.

**Objective:**

The aim of the study is to explore the impact of digital health education on the stress, anxiety, and depression levels among PCOS patients in Bangladesh.

**Methods:**

A single blinded, randomized controlled trial was being conducted at the Enayetpur of Sirajganj district at Khwaja Yunus Ali Medical College and Hospital. A total of 212 participants were randomly assigned to either the intervention group or the control group in the study. The intervention group received PCOS related health education via a mobile application reinforced with app notifications and bi-monthly phone calls from the researcher. Baseline Data collection was completed in April 2025. Endline data collection started in November 2025. The intervention was a six-month intervention that ran from May to October. The primary outcome, depression, stress and anxiety was measured using the DASS21 questionnaire. The secondary outcomes were serum hormone levels (cortisol and testosterone), body mass index (BMI), and knowledge about PCOS.

**Results:**

The baseline data collection was completed in April 2025. A total of 212 patient provided their consent to participate in the study. The participants were divided into groups of 106 individuals for the control and intervention groups.

**Trial registration:**

Japan Registry of Clinical Trials (jRCT2062240073), https://jrct.mhlw.go.jp/en-latest-detail/jRCT2062240073 and North South University Institutional Review Board approved this study (#2024/0RNSU/IRBII 002).

## Introduction

1.

Polycystic ovarian syndrome (PCOS) is an endocrine disorder with reproductive outcomes that has a global prevalence of 5%–20% among women [1],[2]. Patients who have PCOS suffer from irregular menstruation, acne, excessive body and facial hair, infertility, metabolic disorder, diabetes, heart disease and emotional instability. All these symptoms cause stress in patients, which subsequently leads to depression and anxiety [3]. Moreover, stress leads to a rise in cortisol level, which adversely affects the metabolism and cognitive functions [4],[5]. Additionally, the levels of testosterone and prolactin hormones are often increased considered to be closely related to the condition of PCOS. Increased testosterone causes hirsutism, acne, and male pattern hair loss, while increased prolactin causes decreased ovulation [6],[7].

Among these symptoms, infertility has a strong impact on the quality of life of the patients. Decreased ovulation and increased testosterone are related to infertility of patients with PCOS [8]. Infertility itself comes with immense stress, both psychologically and socially. Having PCOS along with infertility is a double disease burden that affects a woman's overall physical and mental health [9]. Although patients receive PCOS related symptomatic treatments from gynecologists, lifestyle modifications and behavior changes are equally important for the patients [10].

Currently, treatments of PCOS are limited to symptom specific treatments. The main treatment options are lifestyle modification, diet, and weight management [11],[12]. Albeit many harmful health impacts, the disease is being ignored in terms of awareness among the patients who are suffering every day [13]. This leads to compromised health conditions and immense psychological adverse outcomes, which lead to a poor quality of life [14].

In Bangladesh, women and girls of reproductive age with the condition are unaware of the disease and are left undiagnosed [15]. Women and girls receive medical treatments solely based on medications but not on lifestyle modifications [16]. Even though the body and mind are not separate entity, when it comes to patients' health, physical health tends to receive attention and priority, whereas mental health is mostly left undiagnosed or even unnoticed [17].

With the advancement of technology, many healthcare facilities and healthcare options are accessible to people. A diverse range of social media platforms provides an abundance of information. However, misinformation is not uncommon [17]–[19]. It is important to receive information that is structured, scientifically proven, and professionally approved [20]. This study aims to elucidate the effectiveness of digital health information on a patient's health, both physical and mental. The combined approach of lifestyle modification and traditional medical treatments may also help health professionals to utilize digital technologies to manage and educate patients.

The secondary outcome of this study, serum cortisol and testosterone levels, are commonly associated with psychological stress, which is the primary outcome of this study [21]. While studies showed that cortisol promotes abdominal fat accumulation and slows down weight loss, elevated testosterone contributes to male pattern baldness, hirsutism, and adversely affects a woman's appearance [22],[23]. Body image concerns play a vital role in increased psychological distress [24].

We hypothesize that health education through a smartphone-based application intervention will significantly reduce the levels of stress, anxiety, and depression among PCOS patients compared to usual treatments.

Additionally, our study hypothesizes that digital health education interventions will encourage lifestyle related behaviors that may reduce the testosterone and cortisol levels and eventually improve the depression, anxiety, and stress related to PCOS.

## Materials and methods

2.

### Design

2.1.

This is a hospital-based intervention study that is prospective in nature and has two arms (1:1). This is a single blinded, single centered study where the participants were divided into either an intervention group or a control group. The participants were recruited from a rural private hospital of Bangladesh. The randomized controlled trial design strictly adheres to Consolidated Standards of Reporting Trial (CONSORT) [25] guidelines along with the Standard Protocol Items: Recommendations for Interventional Trial (SPIRIT) [26] guidelines. A schematic overview is shown in Figure 1.

**Figure 1. publichealth-13-01-007-g001:**
[figure not shown]
Participant recruitment flowchart.

### Study setting and eligibility criteria

2.2.

The study participants were selected from Enayetpur, which is under the administrative and demographic surveillance jurisdiction of Belkuchi Upazila in the Sirajganj District, within the Rajshahi Division of Bangladesh. To be eligible, the participants had to be women aged 18 or older who were diagnosed with PCOS based on the Rotterdam criteria, which includes oligo/anovulation, hyperandrogenism, and polycystic ovaries. Additional requirements included having access to a smartphone, the ability to read and write in Bengali, and provided informed consent for their participation in the study.

The exclusion criteria included having a serious medical condition, any previous history of psychiatric illness, participants who took psychiatric medications, participants with extremely severe Dass21 scores, participants who were pregnant, or participants with a history of chronic diseases such as heart, kidney, or respiratory illnesses.

### Randomization

2.3.

A simple randomization technique was performed where a computer-generated random number sequence was used for randomization and numbering. Randomization table preparation, where the study ID was placed along with the assigned intervention to sequentially numbered and sealed envelopes, was performed by an independent statistician who was not involved in the study. Additionally, the statistician made the randomization schedule. These envelopes were matched with the serial number of the PCOS participants and securely stored in an office locker. Group assignments of the control and intervention were concealed in identical and sealed envelopes. The envelops were opened at the time of participant enrollment, which occurred after the patient provided informed verbal consent and was assigned a study ID.

### Study activities and content

2.4.

To measure the stress, anxiety, and depression levels, baseline data collection was performed with the DASS21 questionnaire, which was developed by Lovibond and Lovibond (1995) [27]. The DASS21 questionnaire is a measurement scale for depression, anxiety, and stress, and is comprised of 21 questions. Studies tested DASS21 for reliability and validity with Cronbach's alpha reliability test for both clinical and non-clinical samples. The original version consisted of 42 items (DASS) and the short version consists of 21 items (DASS-21). The Bangla version of DASS21 was validated after using the translated questionnaire among medical students of Bangladesh [28]. DASS21 uses a self-reported scale of three sets of 7 items each, and is designed to measure the depression anxiety and stress. The depression scale evaluates dysphoria, hopelessness, devaluation of life, self-deprecation, lack of interest, anhedonia, and inertia. The anxiety scale measures autonomic arousal, muscle effects, situational anxiety, and anxious affect. The stress scale gauges chronic nonspecific arousal, difficulty relaxing, nervous arousal, and tendencies to be easily upset, agitated, irritable, over-reactive, and impatient [29],[30].

The patient's cortisol level, testosterone hormone level, and BMI were checked at baseline and at endline. The knowledge level of PCOS was evaluated in baseline and at the endline follow up using a validated knowledge questionnaire used in previous studies [20]. The endline data was collected after six months following the intervention.

The questionnaire was translated into Bangla and back-translated to English by the researcher. Then, the developed questionnaire was pretested among diagnosed PCOS participants selected from the gynecology department to check the feasibility, reliability, and validity of the questionnaire as a pilot. This was performed by the researcher and two research assistants. After resolving all issues, the finalized questionnaire was used to collect the data of the randomly recruited participants.

Testosterone (TT), Cortisol, BMI, and waist circumference were measured both in baseline and endline, which is 6 months after the baseline measurement.

The data is collected for both the intervention and control groups.

Two research assistants who were trained by the researcher, collected the data.

From the intervention group, a total of 20 participants were purposively selected to participate in the qualitative component of the study. These participants were chosen from those who completed the full 6-month intervention.

The purpose of the qualitative interviews is to explore barriers and facilitators to using the app and engaging with the intervention along with the contextual factors influencing app usage. An one-on-one; in-depth interview will be conducted with the selected participants via an audio call. All interviews will be audio-recorded using a call recording application, with the participants' consent, to ensure accurate data capture for the subsequent analysis.

Table 1 shows the intervention and control group process for 6 months.

**Table 1. publichealth-13-01-007-t01:** Study process throughout 6 months.

Schedule	Intervention group	Control group
Baseline sessions	Interview Administered questionnaire Laboratory test (cortisol and testosterone) Smartphone app education Following up phone call from researcher for 6 months	Interview Administered questionnaire Laboratory test (cortisol and testosterone)
Final session	Interview Administered questionnaire Laboratory test (cortisol and testosterone)	Interview Administered questionnaire Laboratory test (cortisol and testosterone)

### Training of the research assistants

2.5.

Two research assistants were responsible for obtaining informed consent, conducting physical examinations, interviewing the participants, installing the app on the phones of those in the intervention group, and guiding them on how to navigate the lessons and understand the PCOS-related health education content. The principal investigator provided comprehensive training for the research assistants, thereby covering both the general and role-specific aspects of the study. General training included the study background, contact details, study structure, and use of technology, while role-specific training focused on recruitment, consent procedures, data collection, electronic data entry in the KOBO toolbox (Kobo toolbox is an app for data collection from fields), storing and having paper forms that can be used as back up, and checking the data and self-evaluation forms for complete data submission. After training, they were evaluated through practice sessions and role-playing in a private setting. The research assistants were both intern doctors at the same hospital and received support from the gynecologist for the participant's referral, selection, and recruitment. Additionally, they were responsible for showing the study participants how to use the app and explaining the contents of the lesson.

### Intervention group

2.6.

A smartphone app (mHealth) that contained 11 lessons, in which two of these featured videos, one presented a storytelling approach to explain PCOS, and the other demonstrated simple home exercises, was installed in the intervention group patients' phones for PCOS related health education. The lesson topics, which focused on PCOS knowledge, are attached as a supplementary file. All app content, including the videos, were delivered in Bengali to ensure accessibility and better understanding for the participants.

The digital health education app contents were completed based on the current evidence and clinical guidelines for PCOS management. Together, the lead researcher, one gynecologist, one nutritionist, two research assistants, supervisors, authors, and co-authors reviewed the contents for cultural appropriateness, medical accuracy, and clarity.

### Adherence to intervention

2.7.

The study maintained monthly follow-ups, during which the lead researcher contacted the participants in the intervention group. This regular engagement supported the participant's adherence to the intervention. Additionally, if a participant missed a scheduled reminder call from the researcher, the research assistants followed up with supplementary calls to ensure continued participation and compliance.

### Control group

2.8.

The control group received usual medical treatments from the gynecologist and were followed up with 6 months after the study period for the endline measurements.

### Sample size and power

2.9.

The sample size was calculated using G* power (version 3.1) for a repeated-measures analysis of variance (ANOVA) with a within-between interaction (F tests). The following parameters were used: two groups, two measurements, non-sphericity correction ε = 1.0, α = 0.05 (Type I error), and power = 0.80 (Type II error = 0.20).

The effect size f = 0.2319 was derived based on prior literature and our study design. Specifically, a previous study reported a Cohen's d of 0.44 [31] for similar outcomes. In our two-group repeated-measures design, the corresponding unadjusted effect size was calculated as follows:

f=d/2=0.44/2=0.22.

We planned to adjust for baseline covariates in the analysis. Assuming that covariates explain 10% of the variance in the outcome (ρ² = 0.10), the adjusted effect size is as follows:

$${\text{f}}_{\text{adj}}=0.22/\surd 1-0.10=0.2319.$$

Using these parameters in G*Power (F tests, repeated-measures ANOVA, within–between interaction), the calculated total sample size required to detect the prespecified effect size with 80% [32] power at α = 0.05 was 148 participants. To account for an expected 20% [33] attrition rate, the sample size was inflated as follows:

$${\text{N}}_{\text{adjusted}}=148/1-0.20=185.$$

Thus, the final recruitment target was 185 participants (93 in the intervention group and 92 in the control group) to ensure sufficient power for the primary analysis.

### Blinding

2.10.

The participants were blinded to the intervention, while the researchers were aware of the group assignments, including enrollment into the intervention and control groups.

The intervention group received the smartphone application and bi-monthly follow-up calls, while the control group continued their usual care. Because the participants did not know whether they belonged to the intervention or control group, blinding at the participant level was maintained.

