## Limitations

12.

Despite its strengths, the study has several limitations. The participants were recruited from a single hospital in the Sirajganj district, thus limiting the generalizability of findings to the broader rural PCOS population. Additionally, there was a potential risk of information “spillover” to the control group through patient interactions, although verbal agreements were secured from the participants to minimize this effect. The study explored digital health education delivered via a smartphone app in a rural region of Bangladesh, where most women did not personally own smartphones. This presented a challenge, as low levels of digital literacy slowed the recruitment process. To address this limitation, the researcher conducted monthly follow-up calls to the participants as part of the intervention. Moreover, due to financial and time constraints, the six-month follow-up may not capture the complete long-term effects of the intervention.

Furthermore, since DASS21 is a self-reported measure, it introduces the possibility of response and recall bias, as the participants may underreport or overreport their psychological symptoms based on perceived expectations or social desirability. Although cortisol and testosterone biomarkers partially mitigate this limitation, future studies should consider clinician-rated, ecological momentary assessment tools to strengthen the validity.

Future research should include multi-site randomized controlled trials to improve the generalizability and assess scalability across diverse populations. Incorporating a cost-effectiveness analysis would provide important insights for policymakers and healthcare planners regarding the economic feasibility of implementing digital health education programs for women with PCOS. Moreover, longitudinal designs which assess sustained behavioral and psychological changes beyond the intervention period are warranted.

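### Section 2.10 claims that participant blinding was maintained, but its own description of the two arms contradicts this, so the single-blinded label is wrong as written.

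*Protocol article*

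**What the plan says.** The title, the Abstract (Methods) and section 2.1 call the trial single blinded. Section 2.10 says who is meant: "The participants were blinded to the intervention, while the researchers were aware of the group assignments". It then describes the arms: "The intervention group received the smartphone application and bi-monthly follow-up calls, while the control group continued their usual care". The next sentence concludes: "Because the participants did not know whether they belonged to the intervention or control group, blinding at the participant level was maintained".

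Other sections fill in what each woman saw:

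- Section 2.8, on the comparator: "The control group received usual medical treatments from the gynecologist". No sham app, alternative app or matched calls are described there, in Table 1 or in section 6.
- Section 2.5 gives two research assistants several duties, among them "interviewing the participants, installing the app on the phones of those in the intervention group" and coaching in its use. Section 2.4 says two research assistants collected the data.
- The Abstract adds app notifications, and section 2.7 adds follow-up calls by the lead researcher to the intervention group.
- Section 3 says all participants were informed of the study's purpose before enrolment.
- Section 12, on spillover of information to controls, says "verbal agreements were secured from the participants to minimize this effect".

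The primary outcome (section 2.11) is improvement on the DASS-21, which sections 2.4 and 12 call self-reported. Table 1 lists "Interview Administered questionnaire" at the baseline and final sessions. Section 12 grants that answers may be distorted by what participants think is expected or socially acceptable, and offers cortisol and testosterone as partial mitigation.

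**The concern.** Participants are the only party claimed to be blind. If that claim fails, nobody involved in producing the primary outcome is described as blinded.

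This matters most for a self-reported scale, because the respondent is in effect the outcome assessor and her knowledge of her arm enters the measurement directly. Women who were taught the app and telephoned for six months may report fewer symptoms to the people who taught and called them. Such a shift would probably favour the app, and the analysis could not separate it from a true effect. Randomisation, intention-to-treat analysis and multiple imputation do not address it.

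Readers and evidence synthesisers use the blinding label when they judge risk of bias, so a wrong label overstates the strength of the primary result.

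**Working it through.** **Step 1: the blinding claim against the design**

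| Party | What the article says | Blind? |
|---|---|---|
| Intervention women | App installed and taught (2.5), notifications (Abstract), calls (2.7, 2.10) | No: they know what they received |
| Control women | Usual care, no sham (2.8); told the study's purpose (3) | Not established either way |
| Researchers | Aware of assignments (2.10) | No |
| Research assistants | Install and teach the app (2.5), collect the data (2.4) | No |

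The reason given in section 2.10 is that women did not know their group. That cannot hold for those given the app. Blinding of one arm alone, even if it occurred, is not participant blinding.

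**Step 2: the plan's own figure**

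The only design calculation is the sample size. With f = 0.22/√0.90 = 0.2319, a noncentral F test with 1 and N − 2 degrees of freedom and λ = f²N gives power 0.800 at N = 148; 148/0.80 = 185. The stated figures reproduce under that convention. The blinding point does not depend on them.

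**Step 3: how much a reporting shift could matter (illustration)**

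Inputs from the article: 212 enrolled, 1:1 (section 10); 20% expected attrition and planning effect d = 0.44 (section 2.9); two-sided α = 0.05 (section 4). Assumed, because the article gives no value: a differential shift b of 0.1 to 0.3 SD in one continuous DASS-21 score, no true effect, normal approximation.

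- Evaluable: 212 × 0.80 = 169.6, taken as 169.
- SE of the standardised difference = 2/√169 = 0.154.
- Rejection probability = Φ(b/SE − 1.96) + Φ(−b/SE − 1.96).

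| Shift b (SD) | About 169 evaluable | All 212 (SE = √(2/106) = 0.137) |
|---|---|---|
| 0 | 5% | 5% |
| 0.1 | 10% | 11% |
| 0.2 | 26% | 31% |
| 0.3 | 50% | 59% |

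A shift of 0.2 SD is 0.2/0.44 = 45% of the planning effect.

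**The case against.** The strongest reply leaves the core alone and limits what may be built on it.

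- **Mode of the DASS-21.** A reader might infer that the assistants administered the scale by interview. The Table 1 entry suggests this, but the table was flattened in extraction and may hold two separate items, and the text calls the scale self-reported. No sentence states how it was completed. Interview administration is implied, not stated. That the same two assistants interview, collect data and deliver the app is explicit.
- **Controls.** A reader might infer that every participant knew her arm. Section 3 mentions the study's purpose, not the arms, and section 12 does not say who gave the spillover agreements or what they were told. Controls may not have known that an app existed. This stands, but it cannot blind the intervention arm.
- **Response bias ignored?** It is not: section 12 names response and recall bias. The fair criticism is narrower. That text does not link the bias to knowledge of allocation, and its mitigation consists of secondary outcomes, which cannot protect the DASS-21 comparison.
- **Size.** The same assistants see both arms, so social desirability common to both cancels; only the differential part matters. Its direction is likely rather than certain, and no figure in the article supports 0.1 to 0.3 SD. The planned analysis also keeps all randomised women with imputation, so 169 is not the analysis set. The second column above covers that case.

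**Conclusion.** The point holds in this form. The statement that participant blinding was maintained is contradicted by the design that the same section describes. At least the intervention arm and the staff who delivered the app and collected the data were aware of allocation, no other party to the primary outcome is described as masked, and single blinded is wrong as written. This needs no assumption and should be corrected.

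The consequence for the result is a risk of bias of unknown size. The rates of 10%, 26% and 50% show what an assumed differential shift would do. They do not estimate this trial's false-positive rate. The documents do not support the stronger readings that the DASS-21 was certainly interviewer-administered, that controls certainly knew their arm, or that the result will be biased.

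**What to change.** 1. Describe the trial as open-label, with participants and researchers aware, in the title, the Abstract and sections 2.1 and 2.10, and in the results report. Delete the sentence saying that blinding was maintained.
2. Extend the limitation in section 12: the self-reported primary outcome was collected with knowledge of allocation, by staff who delivered the app, and this may bias the comparison toward benefit. Say that the biomarkers do not remove this risk from the DASS-21 comparison.
3. Section 10 says analysis has not started, so mask the arm codes for whoever runs the primary analysis. This is a cheap addition; it protects analytic choices, not the reporting of symptoms.

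These cost wording and a recoding step, with no added visits or staff.

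Optional only: self-completion of the DASS-21 at endline visits still open, in both arms from the same date, with the mode recorded. It is feasible because eligibility requires "the ability to read and write in Bengali". The trade-off must be stated. Endline began in November 2025, so the mode may differ from baseline and from earlier endline visits for a change-from-baseline outcome. Mode may also be confounded with visit date and, if return dates differ, with arm. It would reduce the assistants' influence on answers but leave participants' knowledge of their arm unchanged. For data already collected, only relabelling and disclosure remain.
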